#### Recruitment and implementation

Investigators and trained research assistants will participate in the enrollment of participants in accordance with the inclusion criteria (Fig. 1). Neonates will be recruited every day around the clock consecutively until sample size is reached. Data from babies will be used in the trial only after written parental consent is given. A senior investigator will be available at all times to discuss concerns raised by parents or clinicians during the course of the trial.

**Fig. 1 Fig1:**
[figure not shown]
Trial profile (CONSORT flowchart)

#### Tagging of newborns

All neonates enrolled in the trial and their mothers will be tagged with a trial bracelet with a unique trial ID number to facilitate matching and retrieval.

#### Randomization

Cluster randomization will be used, choosing day-by-day clusters. For practical reasons, individual randomization is not feasible, so all neonates enrolled in the same day (representing a cluster) will be randomly assigned to the same treatment. This approach randomly assigns daily groups of neonates rather than individual neonates, and neonates within any one day are likely to respond in a similar manner; hence, their data cannot be assumed to be independent. The clustering structure of the data was taken into account in sample size calculation and data analysis planning. A randomization list will be made by an independent statistician using block randomization with block sizes of 4–8. The allocation remains concealed until the actual trial day when the randomization envelope is opened by the surveillance officer on duty at 8 a.m. The midwives are informed at the beginning of each shift of the assigned treatment. The envelopes and assignment cards are discarded after use. The assigned procedure will then be performed until the next randomization. To provide proper PPV to the baby, the American Heart Association and European Resuscitation Council guidelines recommend switching to a supraglottic airway device if the resuscitator considers that the FM is failing [17]. We recommend the resuscitator to optimize the ventilation during 3 mins before considering switching ventilation option from FM to i-gel and vice versa, to keep contamination between arms low.

#### The intervention

Oral consent will be sought for all mothers admitted to the delivery unit, followed by deferred written informed consent as soon as practicable for mothers of babies eligible for the trial. HBB principles of the golden minute will be applied to all babies not crying at birth, including drying, stimulation, and assessment. A stopwatch will be started at the time of birth by a research assistant for all eligible participants. In the case of “baby is not breathing” after initial steps, the midwife will immediately (after cutting the cord) move the babies in need of PPV to the resuscitation area. Inflations will be administered with room air at a rate of 40 to 60/min with a 240-mL silicon self-inflating bag and a pop-off valve limit at 35 cm H_2_O (Laerdal Medical). Silicone, round-shaped FM (size 1, Laerdal Medical) or i-gel^®^ (size 1) will be available at each delivery. The duration of resuscitation will be defined as the time period from start of ventilation to the establishment of spontaneous breathing. Heart rate will be registered with a dry-electrode electrocardiogram monitor (NeoBeat Newborn Heart Meter, Laerdal Global Health, Stavanger Norway) featuring fast signal acquisition [39]. All babies with a 5-min APGAR (Appearance, Pulse, Grimace, Activity and Respiration) score of less than 7, respiratory distress, hypothermia (axillary temperature of less than 36.0 °C), or signs of encephalopathy will be transferred to the NICU. Resuscitation data, any contamination between arms, follow-up contact, and admission to the neonatal unit will be recorded by a research assistant. All interventions will be recorded on video to ensure quality assurance and data collection.

#### Management from supervising physician

Advanced resuscitation can be initiated in accordance with local hospital and International Liaison Committee on Resuscitation (ILCOR) guidelines [34], should a supervising physician be available. This can include use of alternative airways, including ETT, chest compressions, and drug administration.

#### Contamination between arms

Contamination between arms (switching to the alternative device) will be possible after 3 min of sustained PPV, should ventilation be deemed unsatisfactory. The alternative device will be accessible in an easily accessible box on the resuscitation table. This possible scenario will be practiced during the training. In all cases, a report specifying the reasons for switching to the alternative airway device will be filled out.

#### Masking

Health-care providers (midwives) performing resuscitation and the research assistant recording resuscitation data in the delivery ward cannot be masked to the allocation arm. However, the examiners assessing neonatal encephalopathy outcomes will be masked to the arm allocation. Outcome examiners will be exclusively working at the NICU, physically separated from where the resuscitations are performed. The arm allocation will not appear on the medical chart. Thus, arm allocation of admitted patients will not be identifiable by the outcome examiner. The independent data monitoring committee (IDMC) will have access to arm allocation when performing interim analysis and assessment of AEs/SAEs. The statistician who will perform data analysis will be masked to treatment allocation.

### Sample size

Considering our previous phase II trial, we estimate that a reduction of 25% of adverse outcomes may be possible. A sample size of 954 participants (477 per arm) is required to have a 90% chance of detecting, as significant at the 5% level, a decrease in the primary outcome measure from 40% in the standard-of-care arm to 30% in the supraglottic-airway arm. The sample size is increased to 1150 or 1240 because of the day-by-day cluster randomization, assuming an intra-class correlation of 0.10 and an average daily enrollment of three or four participants, respectively.

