**Methods:**

A randomized phase III open-label superiority controlled clinical trial will be conducted at Mulago Hospital, Kampala, Uganda, in asphyxiated neonates in the delivery units. Prior to the intervention, health staff performing resuscitation will receive training in accordance with the Helping Babies Breathe curriculum with a special module for training on supraglottic airway insertion. A total of 1150 to 1240 babies (depending on cluster size) that need positive pressure ventilation and that have an expected gestational age of more than 34 weeks and an expected birth weight of more than 2000 g will be ventilated by daily unmasked randomization with a supraglottic airway device (i-gel^®^) (intervention group) or with a face mask (control group). The primary outcome will be a composite outcome of 7-day mortality and admission to neonatal intensive care unit (NICU) with neonatal encephalopathy.

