### Statistical analysis

A detailed statistical analysis plan—based on the principles in this section—will be developed before the statistical analysis of the trial. Data analysis will be performed by using the statistical software packages Stata, SAS, and R. All tests will be two-sided, and a *P* value of less than 0.05 will be considered statistically significant. Missing data will be considered, and appropriate imputations will be discussed and performed when appropriate. Statistical analysis will include an unadjusted analysis followed by an adjusted analysis. The primary outcome will be compared between the two treatment arms by using the chi-squared test. The secondary outcomes will be compared by using the chi-squared test or Fisher’s test (categorical outcomes) and using the Student’s *t* test or Mann–Whitney test (continuous outcomes). Mixed-effect regression models will be estimated to evaluate the effect of the treatment on binary outcomes, adjusting for clusters (random effect) and clinically relevant confounders. Data analyses will be performed on an intention-to-treat (ITT) basis. However, since the trial is prone to some contamination (i.e., the person resuscitating may decide to shift to the other device) which can be limited by appropriate training but not entirely prevented, a per-protocol analysis and a contamination-adjusted ITT analysis will also be performed. These results will be considered along with the primary ITT analysis when drawing the conclusions of the trial. Subgroup analyses—per treatment center, time of the day (i.e., day/night), and per birth mode—will be carried out with exploratory purpose.

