## Discussion

Newborn resuscitation training and simulation-based curriculum show mixed results in relation to their impact on newborn mortality [3, 4] and their effect on neurological morbidity remains unknown [43]. Further improvement of neonatal resuscitation performance is crucial.

This large trial is the first to assess the impact on mortality/morbidity of the use of a supraglottic airway device during neonatal resuscitation. It is powered to 90% and designed to add evidence lacking in this field. To the best of our knowledge, only four RCTs comparing LMA or supraglottic airway to FM ventilation including 636 patients have previously been published [18, 19, 25, 26, 32]. They have focused mainly on vital sign outcomes or successful resuscitation [34]. Safety and long-term outcomes remain important knowledge gaps. This task-shifting intervention involves midwives as they are the frontline health workers in many settings where newborn mortality is high. The burden of disease from intrapartum-related events can be reduced if simple and robust technologies for newborn resuscitation can be identified [44].

The trial will also monitor neonatal outcome data until day 7. We hypothesize that effective ventilation will be easier to perform with the supraglottic airway device and significantly decrease early neonatal mortality and brain damage from neonatal encephalopathy. Results from this large trial will contribute to provide evidence that can help define best practice advice for future guidelines.

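### The stated 90% power holds only for equal daily counts and complete outcomes; at the plan's own ICC it is about 88% if daily counts are Poisson, and about 86% with 5% of outcomes missing

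*Protocol article*

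**What the plan says.** The Sample size section of the protocol article starts from individual randomization. It arrives at 477 babies in each arm, 954 in all, for 90% power with a 5% significance level. The effect to be detected is given as "a decrease in the primary outcome measure from 40% in the standard-of-care arm to 30% in the supraglottic-airway arm". On sidedness, the Statistical analysis section says: "All tests will be two-sided". The total then rises to 1150 or 1240 because treatment is allocated by day, "assuming an intra-class correlation of 0.10 and an average daily enrollment of three or four participants, respectively". The Abstract repeats the two totals as a range that depends on cluster size. The Discussion says of the trial: "It is powered to 90% and designed to add evidence lacking in this field".

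Under Randomization, a cluster is everyone enrolled on one day. Under Recruitment and implementation, enrolment is consecutive, at all hours, until the total is reached. The outcome of babies who are not in hospital depends on an appointment or phone call at day 7 (Assessment and collection of outcomes). Missing data are mentioned under Statistical analysis, but the sample size carries no allowance for them.

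**The concern.** Three or four babies a day is described as an average, but the inflation used is exact only when every cluster has the same size. No one sets how many babies will need ventilation on a given day, so cluster sizes must differ. At a fixed total and ICC, unequal clusters carry less information than equal ones. Outcomes that cannot be obtained reduce it further. Both effects act in the same direction, against a calculation with no slack.

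What is at stake is how the result is read. The Discussion presents 90% power as a property of the trial, and a neutral finding would be weighed against that figure.

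**Working it through.** **Inputs from the protocol.** Event rates 0.40 and 0.30, two-sided 5% level, 90% power, 1:1 allocation, ICC 0.10, mean cluster size m = 3 (total 1150) or m = 4 (total 1240).

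**Inputs assumed here.** The CV of the daily counts and the proportion of missing outcomes. The protocol gives neither.

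**Step 1: reproduce the plan.** The usual two-proportion formula (pooled variance under the null, no continuity correction) gives 477 per arm, or 954. The equal-cluster design effect is 1 + (m − 1) × 0.10:

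- m = 3: 1.2, and 954 × 1.2 = 1144.8 (stated 1150)
- m = 4: 1.3, and 954 × 1.3 = 1240.2 (stated 1240)

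For power, take n = total / (2 × design effect) per arm and z = [0.10 × √n − 1.96 × √(2 × 0.35 × 0.65)] / √(0.40 × 0.60 + 0.30 × 0.70).

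- 1150 / 1.2 = 958 effective babies: 90.2%
- 1240 / 1.3 = 954 effective babies: 90.1%

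The stated figures reproduce. The margin is about 5 babies at three per day and none at four.

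**Step 2: let daily counts vary.** The design effect becomes 1 + [(1 + CV²) × m − 1] × 0.10. For Poisson counts CV² = 1/m, so it reduces to 1 + 0.10 × m.

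| Assumed spread | Design effect, m = 3 | Power at 1150 | Design effect, m = 4 | Power at 1240 |
|---|---|---|---|---|
| Equal counts | 1.200 | 90.2% | 1.300 | 90.1% |
| CV 0.3 | 1.227 | 89.5% | 1.336 | 89.3% |
| CV 0.5 | 1.275 | 88.4% | 1.400 | 87.8% |
| Poisson | 1.300 | 87.8% | 1.400 | 87.8% |
| CV 0.8 | 1.392 | 85.5% | 1.556 | 84.3% |

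Example for the Poisson row at m = 3: 1150 / 1.3 = 885 effective babies, or 442.3 per arm. Then z = (0.10 × 21.03 − 1.322) / 0.671 = 1.164, which is 87.8%.

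**Step 3: allow for efficient weighting.** The protocol plans mixed-effect models with cluster as a random effect, and these lose less from unequal clusters. Weighting a day of k babies by k / (1 + (k − 1) × 0.10) over the Poisson distribution gives effective design effects of 1.278 and 1.372. Power is then 88.3% and 88.4%.

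**Step 4: assume 5% of outcomes are missing.**

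- Equal counts: 88.7% at 1150 and 88.5% at 1240.
- Poisson counts: 1150 × 0.95 / 1.3 = 840 effective babies, which is 86.1%. 1240 × 0.95 / 1.4 = 841, also 86.1%.
- Poisson counts, if the loss is also taken to shrink the clusters: 86.5% and 86.6%.
- Poisson counts with the weighting of step 3: 86.7% and 86.8%.

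**The case against.** The strongest reply is that nothing has been miscalculated: every stated figure reproduces, and the text does say average. That stands. The fault lies in the fit of the formula to the design, not in the arithmetic.

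A second reply is that the spread and the loss rate are supplied by this review. That also stands. Variation as such does not produce 88%; a Poisson spread does, and a milder one costs less than a point. Admitted babies are followed daily in the unit, so loss could be small. Imputation is foreseen, although it would restore little information about an outcome that was never observed.

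A third reply is that the ICC is itself uncertain and may be lower. Under Poisson counts the totals would again give 90% at an ICC of about 0.07: (1150 / 954 − 1) / 3 = 0.0685 and (1240 / 954 − 1) / 4 = 0.075. But that replaces the plan's own input, and a higher ICC would push the other way. It does not support the 90% stated at 0.10.

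Two stronger readings are tempting. One is that babies without written consent further reduce the analysed number, since "Data from babies will be used in the trial only after written parental consent is given". The protocol does not show this. Consent is an inclusion criterion and recruitment continues until the total is reached, so such babies can be replaced. The other is that switching between devices dilutes the effect and lowers power again. The protocol expects some switching, but it gives no rate and does not say whether the 10-point difference already allows for it. No figure can be attached.

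**Conclusion.** The point holds in a limited form. The flat 90% in Sample size and Discussion assumes equal, or very nearly equal, daily counts and complete outcomes, and the design cannot deliver equal counts. At the plan's ICC of 0.10 the direction of the shortfall is certain and its size is modest: about 2 points for Poisson counts (somewhat less with mixed-model weighting) and about 4 points if 5% of outcomes are also missing. Across a CV of 0.3 to 0.8, with no loss, power runs from about 89.5% down to 84.3%.

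A reader might infer that the sample size is wrong or that the trial must be enlarged. Neither follows. The totals are correct on their own inputs, and moving from 1150 to 1240 at three per day would mean enrolling 90 more babies to meet assumptions the protocol does not make. What needs correcting is the power claim.

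**What to change.** In Sample size and in Discussion, replace the unqualified 90% with a conditional statement. For 40% against 30% at an ICC of 0.10, power is about 88% if daily counts are Poisson, and about 86% if 5% of outcomes are also missing. Give the range by assumed CV (about 89.5% and 89.3% at 0.3, down to 85.5% and 84.3% at 0.8, for 1150 and 1240 respectively). State that 90% applies only with equal daily counts and complete outcomes.

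The cost is a slightly less favourable stated power. No change to enrolment, design or analysis is involved.

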### Data collection and monitoring

#### Assessment and collection of outcomes

The primary outcome will be assessed in two parts. Mortality outcome will be collected daily at the NICU for admitted trial patients until day 7. Non-hospitalized participants will receive a scheduled appointment or phone call by a trial nurse with the mother at day 7 assessing the health of the baby. For all hospitalized participants, morbidity by neonatal encephalopathy will be assessed by a trial doctor masked to the arm allocation. This assessment will take place daytime on day 1, 2, 3, 4, and 5 or until discharge, using Thompson score (Table 1).

**Table 1 Tab1:** Timeline of the trial

	Enrollment	Allocation	Admission neonatal intensive care unit		Follow-up
Time point	T-1	Day 0	Day 1	Day 2–5	Day 7
Enrollment					
Eligibility screen	×				
Prior oral consent	×				
Deferred consent			×		
Randomization		×			
Interventions					
Resuscitation		×			
Assessments					
Active monitoring of resuscitation		×			
Video recording		×			
Neurological status			×	×	
Mortality assessment			×	×	×

Data from the pre-coded case report form (CRF) will be entered into Open Data Kit (ODK) (https://opendatakit.org), an open-source suite of tools that helps researchers manage mobile data collection solutions. The data will be stored on an encrypted server and subsequently transferred to a statistical software package for analysis.

The CRFs will be pre-tested before the commencement of the trial. Data from the birth attendants’ questionnaire and the CRFs will be filled in by the birth attendants and will be continuously entered into ODK.

Videos will be recorded as a quality control. The neonatal resuscitation algorithm will be put in place to ensure that all interventions are standardized. A proper light source is needed on the table. Headlamps will act as backup in case of a power shortage at night.

#### Independent data monitoring committee

An IDMC consisting of four members—a statistician, an obstetrician, and two pediatricians—was appointed. They are operating in accordance with the IDMC charter which is developed with the members.

The timing of the interim analysis will be carried out by the IDMC. It will be planned when about half of the events have occurred, following the DAMOCLES (Data Monitoring Committees: Lessons, Ethics, Statistics) group recommendations [40].

The IDMC will ensure that the trial protocol was followed and control the adequacy of enrollment and randomization. The interim data will also assess quality standards and adherence to ethical requirements.

The interim analysis will be performed by the IDMC statistician unmasked to the treatment allocation. Based on this, the IDMC will make recommendations on the continuation of the trial and its modifications or decide on potential termination in case of harm.

### Statistical analysis

A detailed statistical analysis plan—based on the principles in this section—will be developed before the statistical analysis of the trial. Data analysis will be performed by using the statistical software packages Stata, SAS, and R. All tests will be two-sided, and a *P* value of less than 0.05 will be considered statistically significant. Missing data will be considered, and appropriate imputations will be discussed and performed when appropriate. Statistical analysis will include an unadjusted analysis followed by an adjusted analysis. The primary outcome will be compared between the two treatment arms by using the chi-squared test. The secondary outcomes will be compared by using the chi-squared test or Fisher’s test (categorical outcomes) and using the Student’s *t* test or Mann–Whitney test (continuous outcomes). Mixed-effect regression models will be estimated to evaluate the effect of the treatment on binary outcomes, adjusting for clusters (random effect) and clinically relevant confounders. Data analyses will be performed on an intention-to-treat (ITT) basis. However, since the trial is prone to some contamination (i.e., the person resuscitating may decide to shift to the other device) which can be limited by appropriate training but not entirely prevented, a per-protocol analysis and a contamination-adjusted ITT analysis will also be performed. These results will be considered along with the primary ITT analysis when drawing the conclusions of the trial. Subgroup analyses—per treatment center, time of the day (i.e., day/night), and per birth mode—will be carried out with exploratory purpose.

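### The primary outcome is assigned an ordinary chi-squared test although whole days are randomised; under the protocol's own ICC of 0.10 its true size is about 7.4% or 8.6%, and the planned mixed model is not named as decisive

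*Protocol article*

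**What the plan says.** All of this is in the protocol article.

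- **Randomization.** The unit is the day: "all neonates enrolled in the same day (representing a cluster) will be randomly assigned to the same treatment". The section gives the consequence itself: "neonates within any one day are likely to respond in a similar manner; hence, their data cannot be assumed to be independent". It then gives an assurance: "The clustering structure of the data was taken into account in sample size calculation and data analysis planning".
- **Sample size.** 954 babies (477 per arm) give 90% power at the 5% level for 40% versus 30%. This is raised to 1150 or 1240 for an intra-class correlation of 0.10 and an average of three or four babies per day.
- **Statistical analysis.** Tests are two-sided, with P below 0.05 significant. The order of work is: "Statistical analysis will include an unadjusted analysis followed by an adjusted analysis". For the primary outcome: "The primary outcome will be compared between the two treatment arms by using the chi-squared test". Secondary outcomes get chi-squared or Fisher tests if categorical, and Student's t or Mann-Whitney tests if continuous. Mixed-effect regression models are also planned for binary outcomes, "adjusting for clusters (random effect) and clinically relevant confounders". The section refers to a primary intention-to-treat analysis but does not say which of these tests it means.

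**The concern.** A chi-squared test treats each baby as separately randomised. When all babies of a day share one device and tend to share an outcome, the variance of the difference between arms is larger than the test supposes, so it rejects a true null hypothesis more often than 5% of the time. The design and the sample size recognise this; the test named for the primary outcome does not.

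Two P values will exist for the primary outcome, only one of which respects the design, and both face the same 0.05 threshold. If they fall on opposite sides of it, the protocol does not say which is the trial's answer. The error runs towards claiming a difference that is not there, in a superiority trial meant to inform resuscitation guidelines.

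**Working it through.** **Inputs.** From Sample size: 40% versus 30%, two-sided 5%, 90% power, intra-class correlation (ICC) 0.10, m = 3 or 4 babies per day. From Trial design: 1:1 allocation.

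**1. Reproduce the plan's figures.** Two proportions, pooled variance under the null, no continuity correction:

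n per arm = [1.960 × √(2 × 0.35 × 0.65) + 1.282 × √(0.40 × 0.60 + 0.30 × 0.70)]² / 0.10² ≈ 476.0, rounded up to 477. Total 954, as stated.

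Design effect DE = 1 + (m − 1) × ICC:

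- m = 3: DE = 1.2; 954 × 1.2 = 1144.8 (stated 1150)
- m = 4: DE = 1.3; 954 × 1.3 = 1240.2 (stated 1240)

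The planned numbers therefore presuppose a cluster-adjusted test with equal days.

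**2. Size of the ordinary chi-squared test.** The true variance is DE times the assumed one, so

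actual size = 2 × [1 − Φ(1.96 / √DE)]

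| Babies per day | DE | 1.96/√DE | Actual size |
|---|---|---|---|
| 3, equal days | 1.2 | 1.789 | 7.4% |
| 4, equal days | 1.3 | 1.719 | 8.6% |

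**3. Unequal days (an added assumption).** With varying counts, DE = 1 + [(1 + CV²) × m − 1] × ICC. For Poisson counts CV² = 1/m, so DE = 1 + m × ICC. This gives 1.3 (m = 3, size 8.6%) and 1.4 (m = 4, size 9.8%).

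**4. Sensitivity to the ICC, equal days.**

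| ICC | 3 per day | 4 per day |
|---|---|---|
| 0.01 | 5.2% | 5.3% |
| 0.05 | 6.2% | 6.8% |
| 0.10 | 7.4% | 8.6% |
| 0.15 | 8.6% | 10.4% |

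**5. Simulation under the null.** Beta-binomial outcomes, ICC 0.10, days randomised in blocks, event rate 40% or 30% in both arms, 8000 runs per scenario. The ordinary test rejected in 7.3-7.6% (three per day) and 8.4-9.6% (four per day) of runs with equal days, and in 8.8-9.6% with Poisson days. The Monte Carlo standard error is about 0.3 percentage points. The 9.6% with four equal babies per day looks like simulation noise: exact enumeration of the same beta-binomial model with equal arms gives 8.6-8.7%. A cluster-robust test on the same data rejected in 4.9-5.7%.

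**6. Where the two answers would differ.** Allowing for DE, significance needs an unadjusted |z| above 1.96 × √DE. That is 2.147 (P = 0.032) for DE 1.2 and 2.235 (P = 0.025) for DE 1.3. A chi-squared P between 0.032 or 0.025 and 0.05 would lose significance once clustering is allowed for.

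**7. Power of a cluster-adjusted test at the planned size.** Equal days: 1150 / 1.2 = 958 and 1240 / 1.3 = 954 effective babies, so about 90% in both cases. With Poisson days it would be about 88%.

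**The case against.** The best defence is that a valid analysis is already planned. The primary outcome is binary, so the mixed model with a random cluster effect covers it, and the chi-squared test can be read as the first step of an unadjusted-then-adjusted sequence. This stands in part. A reader might infer that the analysis ignores clustering altogether, and the protocol does not support that. But the chi-squared sentence is the only one that names a test for the primary outcome, and the random effect appears only alongside confounder adjustment. Nothing says the model overrides the chi-squared result.

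A second defence is that the detailed statistical analysis plan will settle this. That is fair for the choice of covariates, which is no finding here. It does not cover the test itself: the article says the later plan will rest on the principles in this section, and the chi-squared test is one of them. This is a method stated, not a detail left out.

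A third is that the larger sample size already handles clustering. It does not. Inflation protects the power of a cluster-adjusted test and leaves the type I error of an unadjusted one unchanged.

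A fourth is that the size of the error is conditional. This stands. The ICC of 0.10 is a planning assumption, and figures above 8.6% at that ICC need day-to-day variation that the protocol does not specify.

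**Conclusion.** Wrong as written. The test named for the primary outcome assumes an independence that the same document rejects, and the planned cluster-adjusted model is not made decisive.

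From the protocol's own inputs, the chi-squared test at nominal 5% has a size of about 7.4% (three per day) or 8.6% (four per day). For any positive ICC it exceeds 5%; by how much depends on the true ICC and on how daily numbers vary.

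Two stronger readings are tempting and should not be drawn. One is that the trial's real error rate is 7-10%. That holds only for the chi-squared test, only at an ICC near 0.10, and its upper end needs Poisson daily counts. The other is that the reported confidence intervals will be too narrow. The protocol specifies no interval from the unadjusted comparison, so there is nothing to measure that against.

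The same defect reaches the secondary outcomes. Binary ones have the mixed model beside their unclustered tests. Continuous ones, such as time to start of ventilation, have only Student's t or Mann-Whitney tests, since the mixed models are stated for binary outcomes alone.

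**What to change.** - Name one day-clustered analysis as the single primary test and state that its P value decides the trial. The already planned mixed model with treatment and a random day effect would serve, as would a GEE with robust standard errors clustered on day.
- Make the plain chi-squared test and the crude percentages descriptive only.
- Use cluster-respecting methods for all secondary outcomes, and add one for the continuous outcomes.

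The cost is a change of wording in the protocol and analysis plan, and P values that are slightly less favourable. No extra enrolment follows, because 1150 or 1240 was already calculated for a cluster-adjusted test with equal days.

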## Methods/design

### Trial design

A randomized phase III open-label superiority controlled clinical trial will be conducted in neonates needing PPV at birth with two parallel groups (1:1 ratio): resuscitation with a supraglottic airway device (i-gel^®^) compared to FM (standard of care).

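### As the protocol is written, continuous secondary outcomes are compared only by tests that ignore the day clusters, because the cluster-adjusted models are limited to binary outcomes

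*Protocol article*

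**What the plan says.** The protocol's Randomization section assigns treatment by day: every infant enrolled on one day gets the same device. It expects infants of the same day to respond alike, concludes that their data may not be treated as independent, and says that both the sample size and the planned analysis allow for this.

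The Sample size section does allow for it: "The sample size is increased to 1150 or 1240 because of the day-by-day cluster randomization". The inflation takes a within-day correlation of 0.10 and three or four infants per day.

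The Statistical analysis section does so only in part. For continuous secondary outcomes it names Student's t "test or Mann–Whitney test (continuous outcomes". The cluster random effect appears in one sentence, which is limited by outcome type: "Mixed-effect regression models will be estimated to evaluate the effect of the treatment on binary outcomes". The significance rule has no such limit: "All tests will be two-sided, and a *P* value of less than 0.05 will be considered statistically significant".

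The Secondary outcome measures section lists two outcomes that are naturally continuous: time to initiate PPV, and heart rate at seven times from 0 to 300 s. A detailed analysis plan is promised, to be built on the principles of the Statistical analysis section.

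**The concern.** Student's t and Mann–Whitney tests take each infant as an independent unit. Here the independent unit is the day. Infants of one day share the assigned device and to some extent the staff on duty, and time to initiate PPV depends directly on the operator, so some within-day correlation is plausible. If it is positive, the tests understate the standard error of the difference between arms.

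This goes beyond a missing detail. The protocol names a method for continuous outcomes, that method conflicts with its own design, and its cluster adjustment stops at binary outcomes. An analysis plan that followed these principles faithfully would carry the conflict forward. At stake is how results for time to PPV and heart rate are read: they would be held to the 5% threshold while the actual false-positive rate is higher.

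**Working it through.** **Inputs from the protocol**
- Two-sided 5% level for all tests (Statistical analysis).
- 90% power, 477 per arm: "A sample size of 954 participants (477 per arm) is required to have a 90% chance of detecting" (Sample size).
- Rates of 40% and 30% (Sample size), with 1:1 allocation (Trial design).
- Intra-class correlation (ICC) 0.10, with 3 or 4 infants per day (Sample size). This is stated for the primary outcome.

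**Not in the protocol:** the ICC of time to PPV or heart rate. I use 0.10 as the reference value and 0.01 to 0.20 as an assumed range.

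**Step 1: reproduce the protocol's own figures.** For two proportions with pooled variance, two-sided, no continuity correction:

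n per arm = [1.960·√(2·0.35·0.65) + 1.2816·√(0.40·0.60 + 0.30·0.70)]² / 0.10² = (1.322 + 0.860)² / 0.01, which rounds up to 477. The total is 954, as stated.

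Design effect: DE = 1 + (m − 1)·ICC.
- m = 3: DE = 1 + 2·0.10 = 1.2; 954 × 1.2 = 1144.8 (stated 1150).
- m = 4: DE = 1 + 3·0.10 = 1.3; 954 × 1.3 = 1240.2 (stated 1240).

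So the protocol itself works with design effects of 1.2 and 1.3.

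**Step 2: error of a test that ignores the clusters.** The true variance of the difference in means is DE times the variance the test assumes, so

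type I error = 2·[1 − Φ(1.960/√DE)].

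- m = 3: 1.960/√1.2 = 1.789, giving 7.4%.
- m = 4: 1.960/√1.3 = 1.719, giving 8.6%.

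Simulated t tests on day-clustered normal data at ICC 0.10 (5000 runs each; 192 days of 3 and 155 days of 4 per arm) gave 7.2% and 8.8%. The simulation error is about 0.4 percentage points, so these agree with the formula.

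**Step 3: width of intervals.** Intervals are too narrow by √DE: √1.2 = 1.10 and √1.3 = 1.14. A nominal 95% interval then covers 92.6% or 91.4% (100% minus the error in step 2).

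**Step 4: range over the unknown ICC**

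| Assumed ICC | Type I error, 3 per day | Type I error, 4 per day |
|---|---|---|
| 0.01 | 5.2% | 5.4% |
| 0.05 | 6.2% | 6.8% |
| 0.10 | 7.4% | 8.6% |
| 0.20 | 9.8% | 12.1% |

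The table takes equal numbers per day. If daily counts varied like a Poisson variable, DE would be 1 + m·ICC, that is 1.3 and 1.4 at ICC 0.10, and the errors would be 8.6% and 9.8%. The simulation covers the t test only; I expect the Mann–Whitney test to err in the same direction.

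**The case against.** The best defence is that the article is a summary. The same section promises an unadjusted analysis followed by an adjusted one without limiting this to an outcome type, and the Randomization section says that clustering was considered in planning the analysis. The t and Mann–Whitney tests could be the unadjusted step, with the model for continuous outcomes left to the analysis plan. This rules out saying that these outcomes will never receive a cluster-adjusted analysis. It does not remove the point: the only adjusted model then described is confined to binary outcomes, and the later plan is to rest on these principles.

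It is also fair that the size is uncertain. The ICC of 0.10 belongs to the primary outcome, and at 0.01 the inflation is negligible.

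A reader might go further and infer that the seven heart rates will be tested one at a time and that their p values are invalid for that reason. The protocol does not support this:
- It lists the time points but does not say that each is tested separately. One summary value per infant would also suit a t test.
- Repeated measurement does not invalidate a single p value. Clustering aside, each test keeps its 5% error. Seven tests would raise questions of multiplicity and efficiency, which an article may leave to the analysis plan.
- Any family-wise figure depends on a correlation that the protocol does not give. For seven tests, clustering aside, it is about 30% if they are independent and about 11% at an exchangeable correlation of 0.9.
- Nor can it be said that infants with a missing reading will simply be dropped, since the section provides for imputation where appropriate.

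**Conclusion.** The point holds for clustering and for continuous secondary outcomes only. As written, the Statistical analysis section gives these outcomes tests that assume independence, in conflict with the Randomization section.

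The effect is anti-conservative and moderate: a type I error of about 7.4% to 8.6% instead of 5%, and intervals too narrow by a factor of about 1.10 to 1.14, if the ICC is 0.10 and days contribute three or four infants. Over an assumed ICC of 0.01 to 0.20 the error runs from about 5.2% to 12.1%.

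The primary outcome is not affected by this point, since it is binary and falls within the mixed models. No conclusion is drawn about multiplicity across heart-rate time points.

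**What to change.** Change the Statistical analysis section so that the cluster adjustment is not tied to outcome type. Suggested wording:

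> Treatment effects on both binary and continuous outcomes will be estimated from mixed models that include randomization day as a random effect. If several heart-rate readings per infant are modelled together, a random effect for infant within day will be added. Student's t and Mann–Whitney tests will be reported as descriptive only.

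Details such as a transformation for skewed times can stay in the analysis plan. With about 1150/3 ≈ 383 or 1240/4 = 310 days, there are ample clusters for such models to hold the error near 5%.

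The cost is slightly more analysis work and somewhat wider intervals (by about 1.10 to 1.14 at ICC 0.10), which reflect the information the design actually provides. No new data are needed.
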